### Data collection

Most patients in the outpatient clinic would be enrolled in the study. We would first obtain the patient’s informed consent. Then, we will collect the patient’s demographic data (sex, age, occupation, home address, diagnosis, and past history of illness) and help the patient fill out the TCM symptom scale to determine the type of symptom presented. A peripheral blood sample would be collected from each included patient prior to the initiation of treatment. The blood sample would be examined for various biochemical parameters such as liver and kidney function, iron metabolism-related indicators, hepcidin levels, and inflammatory factor-related markers. By randomly assigning them into either group, the patients would be administered with oral doses of conventional medicine with YGS or placebo for 3 months (12 weeks). At 1-, 2-, and 3-month intervals, the patients will be followed up in order to determine who among them would be suitable to fill up a new TCM symptom scale form to rate their symptoms, and a fresh peripheral blood samples would be collected (Table 2). Use case record form to collect patient clinical data and test data, and enter the information and data into electronic data capture.

**Table 2 Tab2:**
[figure not shown]
Study schedule for patients

### Efficacy assessment

#### Primary outcome

The primary outcome is the blood hemoglobin level; by comparing it to the baseline level prior to the initiation of treatment, an increase of 10 g/L is considered as an effective treatment outcome.

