## Background

Myelodysplastic syndromes (MDS) are a heterogeneous group of hematologic neoplasms characterized as a clonal disorder of the hematopoietic stem/progenitor cells leading to a host of hematological malignancies. MDS can be manifested as one or more morbid hematopoiesis of the bone marrow hematopoietic cells, ineffective hematopoiesis, and high-risk acute myeloid leukemia transformation [1]. Anemia is the most common clinical manifestation in patients with MDS. Approximately 60%–80% of patients have symptoms of anemia, and nearly 50% of MDS patients have severe anemia with an increased risk for heart and lung failure. Patients with International Prognostic Scoring System-Revised score of ≤3.5 has been categorized as lower-risk MDS subpopulation according to the 2012 International Working Group criteria. According to the European MDS statistics, lower-risk MDS accounts for approximately 70% of the entire MDS population, and most lower-risk MDS patients have symptomatic anemia; therefore, improving anemia and alleviating the symptoms of anemia are the main treatment goals for patients with lower-risk MDS [2].

The clinical treatment of lower-risk MDS anemia has always been a challenging task, despite the development of various treatment methods in Western medicine, including erythropoietin, immunosuppressants (cyclosporine A), immunomodulators (lenalidomide amine and thalidomide), and those undergoing clinical trials. A previous study reported that in patients with MDS anemia treated with the aforementioned drugs, 80–90% still require blood transfusion, and blood transfusion dependence (1 U red blood cell transfusion at least every 8 weeks within 4 months) is negatively related to patient survival [3].

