### Study setting and participants

All adult patients with lower-risk MDS admitted at the respiratory departments in three tertiary care hospitals would be screened and enrolled. Eligible patients would be asked to provide an informed written consent and would be centrally randomized to either the integrated YGS and conventional medicine group or the conventional medicine group. For both groups, all medications would be administered orally for 3 months (12 weeks). Patient recruitment has begun in March 2020 and should be completed in December 2021.

The inclusion criteria are as follows:
Patients aged > 18 years and olderPatients whose peripheral blood cell, bone marrow smear, gene, and chromosome profiles meet the criteria for lower-risk MDS according to the 2020 NCCN guidelines (V1)Patients with a hemoglobin level of < 110 g/LPatients whose symptoms meet the spleen *Qi* deficiency pattern of MDS according to the Standard Criteria for Syndrome Differentiation by TCM[11]

The exclusion criteria are as follows:
Patients who are blood transfusion dependentPregnant or lactating women, and women planning to become pregnant (must undergo urine pregnancy test, a standard test for women of childbearing age, before treatment)Patients with liver and kidney function insufficiency (whose blood aspartate aminotransferase, alanine aminotransferase, or creatinine concentrations exceed the normal value by more than 3 times the upper limit)Patients who recently participated in clinical trials of other drugs (within 2 weeks of TCM, within 7 half-lives of Western medicine)Patients with comorbidities that may cause anemia such as neoplastic diseasesPatients who are unwilling to cooperatePatients who cannot complete the specified observation items after being selected

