### Intervention treatment

All patients would be treated with conventional medicine according to the MDS 2020 NCCN guidelines (V1) and TCM guidelines for the diagnosis and treatment of MDS (2019) [12]. For the conventional medicine and YGS treatment, patients would be given herbal interventions based on the spleen *Qi* deficiency pattern of MDS. YGS is an oral decoction containing five herbs: Ginseng Radix et Rhizoma (*Ren-Shen*), Glycyrrhizae Radix et Rhizoma (*Gan-Cao*), Citri Reticulatae Pericarpium (*Chen-Pi*), Atractylodis Macrocephalae Rhizoma (*Bai-Zhu*), and Poria Sclerotium (*Fu-Ling*). Granules containing these herbs are manufactured by Jiangyin Tianjiang Pharmaceutical Co., Ltd with strict compliance to Good Clinical Practice conditions in terms of the production process and packaging of mixed granules for TCM. Each YGS granule contains 20 g of each herbal raw material (Table 1).

**Table 1 Tab1:** Weight and composition of YGS and placebo granules

Chinese name (*pinyin*)	Latin name	Granule weight (g)	Herbal raw material weight (g)
Yi Gong San granules		**44.8**	
*Ren-Shen*	Ginseng Radix et Rhizoma	6.7	20
*Bai-Zhu*	Atractylodis Macrocephalae Rhizoma	14.7	20
*Fu-Ling*	Poria Sclerotium	6.7	20
*Chen-Pi*	Citri Reticulatae Pericarpium	8.2	20
*Gan-Cao*	Glycyrrhizae Radixet Rhizoma	8.5	20
Placebo granules		**44.8**	0

For the conventional medicine group, patients would be administered placebos containing maltodextrin, lactose, and food coloring, according to the modern pharmaceutical technology and placebo specification for granules. The placebos appear identical to YGS granules in terms of packaging, weight, odor, and color. In all patients, the medications would be administered twice daily, after breakfast and dinner, and up to 3 months (12 weeks).

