### Statistical analyses

A descriptive statistical analysis of all the quantified variables in this study would be performed. The mean, median, and standard deviation will be calculated for quantitative variables, while the absolute and relative frequencies will be calculated for qualitative variables. The SPSS software (version 25.0; IBM Inc., USA) would be used for data processing and analysis. Statistical analysis would be based on the intention-to-treat and per-protocol population principles. The missing data can be processed using the last observation carried forward method. To compare the changes in TCM symptom scores and hematological data of patients before and after taking intervention treatment, multiple comparisons would be performed. A repeat measurement data analysis of variance will be initially conducted followed by a separate effect analysis, including comparisons between groups at each time point, using a multivariate logistic regression model to analyze the correlation between iron metabolism, hepcidin levels, and IL-6, TNF-α, IL-1 expression changes, and curative effect. Additionally, a subgroup analysis can be performed according to the R-IPI, and covariance analysis can be performed considering the factors such as age and sex. A two-sided *P* value of < 0.05 is considered significant.

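### The primary response rule puts no condition on transfusion, so a +10 g/L rise caused by an on-study red-cell transfusion would be scored as treatment response

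*Protocol article*

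**What the plan says.** - **Primary outcome.** "The primary outcome is the blood hemoglobin level". It is compared with the pre-treatment value, and "an increase of 10 g/L is considered as an effective treatment outcome". The sentence asks for no transfusion-free interval and does not say what happens to a transfused patient.
- **Study setting and participants.** Transfusion dependence is an exclusion criterion. Entry requires Hb below 110 g/L, with no lower limit. Nothing is said about transfusion shortly before the baseline sample.
- **Background.** Dependence is described as "1 U red blood cell transfusion at least every 8 weeks within 4 months". The exclusion criterion neither repeats nor cites this description. The same section reports that among patients with MDS anemia on the listed drugs "80–90% still require blood transfusion".
- **Intervention treatment.** Both arms receive guideline-based conventional care. Transfusion is neither prohibited nor mentioned.
- **Statistical analyses.** Intention-to-treat and per-protocol analyses and a repeated-measures analysis of variance are planned, and "The missing data can be processed using the last observation carried forward method". Transfusion is not mentioned.
- **Discussion.** The trial intends to enrol patients who do not depend on transfusion. Western treatment is to be recorded and analysed by stratum.

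**The concern.** A red-cell transfusion raises Hb directly, and it is given after randomisation to patients whose Hb is low. Under an unconditional rule, the patient who did badly enough to need blood can end up classed as a success.

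Randomisation and blinding do not remove this, because the transfusion follows allocation and can depend on how the allocated treatment performed. If YGS works, placebo patients may be transfused more often; their Hb is then propped up and part of the benefit is hidden. The opposite imbalance would flatter YGS. A transfusion shortly before baseline would raise the starting value and make a +10 g/L gain harder to reach.

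The Background also says that transfusion alters hepcidin and eventually causes iron overload, so the iron and hepcidin secondary outcomes are exposed too.

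**Working it through.** **1. Reading the sections together.** The response rule is unconditional. The only transfusion criterion applies at entry and concerns dependence. Concomitant care is not restricted on this point, and the analysis section is silent. An eligible patient transfused during the 12 weeks whose Hb is then 10 g/L above baseline therefore meets the printed definition of effective treatment. Last observation carried forward does not prevent this: a post-transfusion Hb is observed, not missing, and could itself be carried forward.

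**2. Which planning values to use.** Sample size considerations gives gains of 20 and 14 g/L and SD 7 in words, but σ = 14 and δ = 7 in symbols.
- Worded values: 2 × [(1.96 + 0.84) × 7/6]² = 21.3, rounded up to 22. This reproduces the stated 22 per group, without the formula's added μα² term.
- Symbols: 2 × [(1.96 + 0.84) × 14/7]² = 62.7, which does not give 22.

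The worded values are used first and SD 14 is shown alongside.

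**3. Response rates without transfusion.** P(change ≥ 10) = Φ((mean − 10)/SD).
- SD 7: Φ(10/7) = 92.3% and Φ(4/7) = 71.6%; difference 20.7 points.
- SD 14: Φ(10/14) = 76.2% and Φ(4/14) = 61.2%; difference 15.0 points.

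**4. Illustration on the response scale.** The article gives no on-study transfusion rate, so the shares below are assumptions. Observed rate = p + (1 − p) × share of non-responders lifted past +10 g/L.

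| SD | Lifted, YGS / placebo | YGS | Placebo | Difference (points) |
|---|---|---|---|---|
| 7 | 5% / 20% | 0.923 + 0.077 × 0.05 = 0.927 | 0.716 + 0.284 × 0.20 = 0.773 | 15.4 |
| 7 | 10% / 30% | 0.923 + 0.077 × 0.10 = 0.931 | 0.716 + 0.284 × 0.30 = 0.801 | 13.0 |
| 7 | 20% / 5% | 0.923 + 0.077 × 0.20 = 0.939 | 0.716 + 0.284 × 0.05 = 0.730 | 20.8 |
| 7 | 30% / 10% | 0.923 + 0.077 × 0.30 = 0.946 | 0.716 + 0.284 × 0.10 = 0.745 | 20.2 |
| 14 | 5% / 20% | 0.7625 + 0.2375 × 0.05 = 0.774 | 0.6125 + 0.3875 × 0.20 = 0.690 | 8.4 |
| 14 | 10% / 30% | 0.7625 + 0.2375 × 0.10 = 0.786 | 0.6125 + 0.3875 × 0.30 = 0.729 | 5.8 |

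Differences are taken before rounding. With SD 7 the first two rows lose about 26% and 37% of the 20.7 points. The two reversed rows leave the difference almost unchanged, because the YGS arm has few non-responders to lift.

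**5. Illustration on the mean scale.** Observed difference = 6 + L × (share transfused on YGS − share transfused on placebo), where L is the assumed Hb gain from transfusion.
- Placebo transfused more often by 5 points, L = 10: 6 − 0.5 = 5.5 g/L.
- Placebo transfused more often by 20 points, L = 20: 6 − 4.0 = 2.0 g/L.
- The same imbalances reversed: 6.5 and 10.0 g/L.

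With SD kept at 7 and 30 analysed per group, power is 91% at 6 g/L, 86% at 5.5 and 20% at 2.0.

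**The case against.** **Silence is not a rule.** The article never says that transfusion is permitted on study or that post-transfusion Hb counts. Such handling is often left to a full protocol or analysis plan, and neither is shown. That is fair, and on-study transfusion here is an inference. What remains is that the response definition itself is printed, and as printed it classes a transfused patient with +10 g/L as a success.

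**The population may need little blood.** A reader might infer from the Background's 80–90% that most trial patients will be transfused. The article does not support that: the figure concerns treated MDS anemia in general, whereas this trial takes lower-risk, non-dependent patients for 12 weeks. Likewise, the exclusion criterion does not adopt the Background description of dependence, so it is only likely, not stated, that patients transfused less often are eligible.

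**The numbers are assumed.** This stands. A reader might take the 26–37% loss as an estimate of bias; it is not. The 30% placebo scenario moves 0.30 × 28.4% = 8.5% of that arm past the threshold, while under the same model only Φ(−14/7) = 2.3% of placebo patients fall below their baseline. A low starting Hb could still prompt transfusion, but that scenario is towards the high end. Nor can one conclude that a false benefit would arise: the reversed scenarios show none on the response scale, though they would inflate the mean difference.

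**The trial is called pragmatic, and Western treatment is to be analysed by stratum.** Hb under whatever care is given is a recognised estimand, but it does not measure what YGS does to Hb when donor cells contribute. The stratified analysis does not name transfusion, and stratifying on a post-randomisation event would not correct the bias.

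**Conclusion.** The point holds in limited form. The primary response rule is unconditional, only dependence at entry is excluded, and nothing in the article bars transfusion during treatment, so a transfusion-induced rise would be scored as response. The size and direction of the effect on the comparison cannot be determined from the article. The illustrations rest on assumed transfusion shares and gains, on normally distributed changes, and on planning values that the article prints inconsistently (SD 7 or 14). They show that a modest imbalance could matter in a trial of 60, not that one will occur. The amendment should be made because it is cheap and removes a definite misclassification.

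**What to change.** 1. **Response outcome.** Count a patient given red cells between baseline and the month-3 Hb as a non-responder.
2. **Continuous analysis.** Set aside Hb values within a pre-specified window after a transfusion. Handle them in a repeated-measures model that accepts incomplete series, such as a mixed model, and do not carry a value forward. Because transfused patients may be doing worse than the model assumes, add a sensitivity analysis using all observed Hb.
3. **Recording.** Collect transfusion dates and units, including any shortly before baseline, and tabulate them by arm.

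The cost is one paragraph and, if the case report form does not already hold it, one entry for date and units. A few Hb values go unused. Response rates may be slightly lower, and in each arm they can fall by no more than the share of patients transfused. The change concerns analysis and recording only; no change to who is transfused is proposed.

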## Methods

### Objective and design

This multicenter, pragmatic, randomized, and controlled trial is conducted to evaluate the effectiveness of integrating YGS into the conventional treatment for anemia in patients with lower-risk MDS. A total of 60 patients would be recruited and randomly assigned to one of the two treatment groups. During the treatment period, patients in both arms would be followed up for 3 months. The primary outcome (hemoglobin) and secondary outcome measures (TCM symptom score, iron metabolism, hepcidin levels, and inflammatory factors) would be assessed at different points within the trial period.

The study has been approved by the research ethics committee of the Shanghai Baoshan Hospital of Integrated Traditional Chinese and Western Medicine (#201809-01). This trial adhered to the Declaration of Helsinki and has been registered at the Chinese Clinical Trials Registry (ChiCTR1900026774) on October 21, 2019. The trial results would be reported according to the Standard Protocol Items: Recommendations for Interventional Trials statement and the latest version of the Consolidated Standards of Reporting Trials statement.

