### Sample size considerations

Based on the sample size estimation formula (*n*1= *n*2 =2×[(μα+μβ)σ/δ]^2^+ μα^2^), the main research outcome indicator is the change in hemoglobin (Hb) levels, which will be used to estimate the sample size; compared with the baseline results, the Hb level of the experimental group (conventional medicine + YGS) increased to 20 g/L, while the Hb level of the control group (conventional medicine + placebo) increased to 14 g/L (standard deviation: 7 g/L, *n*1=group 1, *n*2= group 2, σ=14, δ=7, bilateral α=0.05, μα=1.96, unilateral β=0.2, μβ=0.84); therefore, each group should comprise 22 patients; considering a 30% loss due to follow-up, each group should comprise 30 patients. Therefore, we intend to recruit 60 patients from March 2020 to December 2021.

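### The primary hemoglobin outcome is not tied to one test: measure, visit and between-arm contrast are all left open, and the 10 g/L criterion does not match the sample-size basis

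*Protocol article*

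**What the plan says.** Four parts of the protocol article bear on the primary analysis.

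- **Primary outcome.** "The primary outcome is the blood hemoglobin level". The same sentence goes on to say that, compared with baseline, "an increase of 10 g/L is considered as an effective treatment outcome". No visit is named, and the comparison described is within the patient.
- **Sample size considerations.** "the main research outcome indicator is the change in hemoglobin (Hb) levels". The assumptions are that "the Hb level of the experimental group (conventional medicine + YGS) increased to 20 g/L" and "the Hb level of the control group (conventional medicine + placebo) increased to 14 g/L", with an SD of 7 g/L, two-sided α of 0.05 and 80% power. The result is 22 evaluable and 30 enrolled per group. The same sentence also prints σ=14 and δ=7.
- **Objective and design.** Primary and secondary outcomes "would be assessed at different points within the trial period". Data collection puts follow-up at 1, 2 and 3 months.
- **Statistical analyses.** A repeated-measures ANOVA comes first, "followed by a separate effect analysis, including comparisons between groups at each time point". A logistic model then relates iron, hepcidin and cytokine changes to curative effect. A two-sided P below 0.05 counts as significant. The section does not say which of these results decides the primary question.

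**The concern.** The article states the primary outcome, the sequence of analyses and the significance level, but together they do not identify one decisive test.

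First, the measure has two forms, a mean change and a response at 10 g/L, and only the mean change has a sample size behind it. Second, three post-baseline visits are compared between groups and none is singled out. Third, the success criterion is set against the patient's own baseline, at a level below what the plan expects on placebo. Reaching it therefore says little about what YGS adds unless the proportions are compared between arms.

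At stake is the trial's main conclusion. With about 30 patients per arm, results may differ between visits and between the two forms of the outcome. The text as written would allow the more favorable one to be reported as primary.

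**Working it through.** **Inputs.** From Sample size considerations: mean changes of 20 and 14 g/L (reading the printed wording as a rise of that size), SD 7 g/L, also σ=14 and δ=7, two-sided α 0.05, power 80%, 22 evaluable and 30 enrolled per arm. From Primary outcome: threshold 10 g/L. From Data collection: three post-baseline visits. Assumed here: changes are normally distributed; between-visit correlation is 0.5 to 0.9 (the article gives none).

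**1. The plan's own figure.** For a difference in means, n = 2×[(1.96+0.84)×σ/δ]². With δ = 20−14 = 6 and σ = 7, n = 2×(2.8×7/6)² = 21.3, rounded up to 22. The stated 22 is reproduced, and power for mean change is 81% at 22 and 91% at 30 per arm. The sample size therefore serves mean change. The printed pair σ=14, δ=7 gives 2×(2.8×14/7)² = 62.7, so 63 per arm, and does not reproduce 22. That conflict is a separate matter, but it means the figures below need a range.

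**2. The threshold against the plan's assumptions.** The expected control rise of 14 g/L exceeds the 10 g/L criterion. P(change ≥ 10) = Φ((mean−10)/SD):

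- SD 7: Φ(10/7) = 92.3% on YGS; Φ(4/7) = 71.6% on placebo.
- SD 14: Φ(10/14) = 76.2% on YGS; Φ(4/14) = 61.2% on placebo.

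**3. Power if response were the primary between-arm test** (exact enumeration of 2×2 tables, two-sided 0.05):

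| SD | n per arm | Chi-square | Fisher |
|---|---|---|---|
| 7 | 22 | 45% | 33% |
| 7 | 30 | 57% | 43% |
| 14 | 22 | 18% | 11% |
| 14 | 30 | 24% | 16% |

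By the normal approximation, 80% power would need 53 evaluable per arm with SD 7 and 149 with SD 14.

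**4. False-positive rate for mean change at three visits.** Simulated under no treatment effect, with 30 per arm, equal correlation between visits and each visit tested at 0.05. The chance that at least one visit is significant:

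- correlation 0.5: 12.4%
- correlation 0.7: 10.7%
- correlation 0.9: 8.2%

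**5. The same with the ANOVA as a gate.** If visit tests count only after a significant group effect, the rate is about 4.5-5%. If either the group effect or the group-by-time interaction opens the gate, it is about 5.5-7%. If a significant group effect or a significant interaction is itself enough for a claim, the rate is about 10%.

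**The case against.** The strongest reply is that the plan is more orderly than this suggests. Sample size considerations calls the change in Hb the main outcome indicator. The ANOVA precedes the visit comparisons, and with a fixed 12-week course and a before-and-after comparison, the end of treatment is the natural time point. On that reading the visit tests only follow up an overall test, and the error rate stays near 5%. This stands in part: the 8-12% is what follows if visits are free-standing, not a certain consequence of the plan. But the article does not call the ANOVA primary or a gate, does not say whether its group effect or its interaction would decide, and names no visit.

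A reader might also infer that the trial is underpowered for its primary outcome. The documents do not support that. No between-arm test of response rates is named; a binary outcome is implied only by the logistic model for curative effect. The power shortfall is conditional on response being taken as primary.

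Nor does it follow that the 10 g/L threshold cannot distinguish the arms. The plan's assumptions with SD 7 imply 92% against 72%, about 20 percentage points apart. The weakness lies in reading the criterion within patients, without a comparison between arms.

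Finally, one might count every secondary outcome at every visit and call for a formal adjustment. Those outcomes are labeled secondary, and multiplicity among them is commonly settled in an analysis plan that is not shown, so it is no part of this point.

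**Conclusion.** The point holds in this form: the article does not fix the primary outcome to one measure, one visit and one between-arm test, and its success criterion does not match the quantity on which the trial is sized. This is more than detail left to an analysis plan, because such a plan would have to choose between the Primary outcome and Sample size sections.

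The size depends on the reading. The false-positive rate is about 8-12% if any visit can carry the claim, and about 5% if the ANOVA group effect is a strict gate. Power is 33-45% at 22 and 43-57% at 30 per arm if response were tested as primary with SD 7, and 11-24% with SD 14. These figures rest on normally distributed changes, on 20 and 14 g/L being rises from baseline, and on assumed correlations of 0.5 to 0.9. That the primary test is left open depends on none of them.

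**What to change.** State one primary test: the between-arm difference in mean Hb change from baseline to month 3 (the end of the 12 weeks), at two-sided 0.05. This matches the existing sample-size basis. Make the proportion of patients with a 10 g/L rise secondary, and say that it is compared between arms. Make the month 1 and month 2 comparisons secondary as well, and state the role of the repeated-measures ANOVA relative to the primary test.

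The cost is a few lines of wording before unblinding, with no further patients or data. The small downside is that a favorable earlier visit or response rate can no longer carry the efficacy claim. If response is preferred as primary, the trial would have to be re-sized.
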